### Participant timeline {13}

#### Enrolment

*Time Point*: Patients will be enrolled *at the time of OHCA *(Fig. 1).*Inclusion Process*: Once a patient meets the inclusion criteria (OHCA, age ≥ 18 years, and undergoing mechanical ventilation), they will be immediately enrolled by the EMS team. The need for informed consent was waived by the responsible ethical committee.

**Fig. 1 Fig1:**
[figure not shown]
Example template of recommended content for the schedule of enrolment, interventions, and assessments. Recommended content can be displayed using various schematic formats. See SPIRIT 2013 Explanation and Elaboration for examples from protocols. **List specific timepoints in this row

#### Interventions

PEEP or ZEEP Intervention:o*Time Point*: Immediately after advanced airway management is secured (using either an extraglottic airway device [EAD] or an endotracheal tube [ETT]).oThe assignment to PEEP or ZEEP is predetermined, as the defined time period dictates whether the patient will receive PEEP (5 mbar) or ZEEP (0 mbar). The sequence of these time periods has been randomized via cluster randomization.oThe intervention will continue throughout the resuscitation efforts until ROSC or cessation of resuscitation efforts.

### Assessments

During resuscitation:oContinuous monitoring of vital signs (e.g., HR, SpO_2_) and ventilation parameters (e.g., PEEP, tidal volume, etCO_2_).Post-resuscitation:o*Time Point*: Immediately upon achieving ROSC until handover at the hospital.o*Measurements*: GCS, vital signs (HR, SpO_2_), and optional initial blood gas analysis will be assessed.Follow-up assessments:o*Time Point*: During hospital stay, including assessments of neurological outcomes and cardiac function (e.g., EKG, vital signs) if applicable.o*Final Assessment*: Date of death (if applicable) or hospital discharge.

### Visits for participants

No formal follow-up visits are required post-resuscitation as all data will be collected during the pre-hospital and hospital phases. The study focuses on immediate outcomes following OHCA and does not include long-term follow-up.

### Sample size {14}

The planned sample size is approximately 600 out-of-hospital cardiac arrest (OHCA) cases, with about 300 patients per group (PEEP vs. ZEEP).

The PerAVent trial is designed as a pilot and feasibility study, primarily aimed at evaluating the practical implementation of PEEP versus ZEEP ventilation in the pre-hospital setting and generating preliminary data for future confirmatory research.

The study hypothesis is that ventilation with PEEP (5 mbar) increases the probability of return of spontaneous circulation (ROSC) compared with ZEEP (0 mbar).

As this is a pilot study, no formal sample size calculation or power analysis has been performed, since no reliable prior data exist on which to base such assumptions. The chosen sample size is therefore based on feasibility considerations and expected case numbers within the participating emergency medical service regions over the planned study period.

The collected data will serve to estimate key parameters—such as recruitment rates, adherence, and effect size estimates—that may inform the design of a future confirmatory trial.

### Recruitment {15}

Recruitment will occur across multiple EMS regions, including Gütersloh, Minden-Lübbecke, and Osnabrück. All eligible OHCA patients treated by EMS teams in these regions during the 12-month data collection period will be enrolled. The large geographic area and population served by these EMS units are expected to provide sufficient participant numbers.

## Assignment of interventions: allocation

### Sequence generation {16a}

In this study, the allocation sequence will be generated using *cluster randomization*. Each participating EMS region (Gütersloh, Minden-Luebbecke, and Osnabrueck) will represent a cluster. The clusters will be randomized to either the intervention group (PEEP) or the control group (ZEEP) using *predefined randomization blocks*, which are based on 6-month intervals. After 6 months, the clusters will switch to the opposite group, ensuring that each region experiences both interventions.

To reduce predictability and maintain the integrity of the randomization, the allocation sequence and any randomization restrictions, such as block sizes, will be managed centrally and will not be accessible to the EMS personnel enrolling participants or assigning interventions. This ensures that the allocation remains concealed until implementation.

### Concealment mechanism {16b}

The allocation sequence will be implemented through a centralized randomization process. The sequence will be concealed from the EMS personnel by utilizing pre-determined randomization blocks that are centrally managed. EMS personnel will not have access to the allocation until the intervention is assigned ensuring allocation concealment throughout the enrolment process. Through regular training sessions, participants will be regularly informed about the assignment within the corresponding time period.

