## Methods: participants, interventions and outcomes

### Study setting {9}

The study will be conducted in pre-hospital EMS settings across multiple regions in Germany. Specifically, the study will involve EMS units from the following districts:GueterslohMinden-LuebbeckeOsnabrueck

With approximately 650,000 inhabitants across all regions combined. These EMS regions serve as the primary sites for data collection, and all resuscitation efforts in OHCA cases in these areas will be included. The study focuses on real-world pre-hospital settings where EMS teams provide critical care during cardiac arrest events before hospital admission.

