## Assignment of interventions: blinding

### Who will be blinded {17a}

In this study, the EMS personnel delivering the interventions (PEEP or ZEEP) will not be blinded, as they need to know which ventilation strategy to apply during resuscitation. Since the patients enrolled in the study are unaware of which group they are assigned to during the resuscitation, they are considered blinded.

However, the outcome assessors and data analysts who evaluate the results, including ROSC probabilities and other clinical outcomes, will be blinded to the group assignments to minimize bias in data interpretation and analysis.

This blinding ensures that the analysis is conducted without any knowledge of which intervention was applied, maintaining objectivity in assessing the study’s outcomes.

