This study faces several practical and operational challenges related to its conduct in a pre-hospital emergency setting. One key issue is the logistics of enrolling patients during OHCA, where time-sensitive decisions must be made. Ensuring that EMS personnel adhere to the study protocol while delivering urgent care will require thorough training and clear communication. Another challenge is the cluster-randomized design, which involves different EMS regions rotating between the PEEP and ZEEP groups. This design requires careful coordination and monitoring to ensure that randomization is properly implemented and that no unintentional crossover occurs between groups. To ensure this, it is planned to program the emergency ventilation modes of the ventilators according to cluster randomization. In addition, regular training sessions and stickers placed on the ventilators are intended to make rescue service staff aware of which group the patient is in at the time of resuscitation.

Additionally, data collection during such high-pressure, fast-paced environments may be difficult. Ensuring accurate and complete documentation of ventilation settings and patient outcomes will be critical. For this reason, it is planned to document the measures taken following the operation using an application-based eCRF. In addition, the emergency respirators will be read out after use so that real-life data on the ventilation settings measured by the respirators is available.

Moreover, variability in care practices across EMS regions may introduce confounding factors that will need to be accounted for in the statistical analysis.

However, the treatment of resuscitation is highly standardized by the regularly updated resuscitation guidelines and the rescue service staff in Germany are regularly re-certified in the performance of CPR in accordance with their legally prescribed further training obligation.

These issues, along with the ethical considerations of conducting research in life-threatening situations, will need careful attention throughout the study.

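### Concealment holds at most for the region-level sequence: crews know the arm before each arrest, entry depends on their starting mechanical ventilation, and no stated analysis compares entry by arm

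*Protocol article*

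**What the plan says.** Concealment mechanism {16b} of the protocol article claims that "EMS personnel will not have access to the allocation until the intervention is assigned ensuring allocation concealment throughout the enrolment process". The last sentence of that section reads: "Through regular training sessions, participants will be regularly informed about the assignment within the corresponding time period". Participants here must mean EMS staff, since patients in cardiac arrest attend no training.

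Other sections describe how the arm is made known:

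- Discussion, on the devices: "it is planned to program the emergency ventilation modes of the ventilators according to cluster randomization".
- Discussion, on labelling: "stickers placed on the ventilators are intended to make rescue service staff aware of which group the patient is in at the time of resuscitation".
- Who will be blinded {17a}: "the EMS personnel delivering the interventions (PEEP or ZEEP) will not be blinded, as they need to know which ventilation strategy to apply".
- Participant timeline {13}, Interventions: the calendar period determines the arm.
- Sequence generation {16a}: "After 6 months, the clusters will switch to the opposite group, ensuring that each region experiences both interventions".

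On entry, Eligibility criteria {10} requires mechanical ventilation via an airway device. Participant timeline {13} has the EMS team enrol the patient once that and the other criteria are met, and Implementation {16c} makes EMS personnel responsible for enrolment. Study setting {9} describes a wider population: "all resuscitation efforts in OHCA cases in these areas will be included". Additional considerations, which follows the eligibility criteria, speaks of an eCRF for every resuscitation case.

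**The concern.** In a cluster trial, open allocation does little harm to the comparison if every patient in the cluster-period enters whatever the staff do. Here one entry criterion is itself a treatment step, taken after the arm is known and by staff who know it. If readiness to connect the ventilator, or the moment of connecting it, differs between PEEP and ZEEP periods, the two enrolled groups can differ in prognosis before PEEP has any effect.

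The intention-to-treat principle does not repair this, because it applies only to those who entered. Nor does enrolling all eligible patients (Recruitment {15}), because eligibility is the step affected. The crossover removes fixed differences between regions, but not behaviour that follows the arm. At stake is the ROSC effect estimate, which Sample size {14} says may inform a future confirmatory trial.

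**Working it through.** **Step 1. Is the arm known before enrolment?** The unit of allocation is a region for six months, and every patient in that region-period has the same arm. Training, programmed devices and stickers tell crews which arm it is. The switch at six months is deterministic, so the second arm follows from the first. The arm is therefore known before each arrest. Sequence generation {16a} claims only that the centrally held sequence stays concealed until implementation. That can be true for the regions before the start, but it does not extend to individual enrolment.

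**Step 2. Does entry depend on the crew?** The ventilation criterion is met only once the crew has placed an airway device and started mechanical ventilation. No section makes that step mandatory. Background and rationale {6a} discusses manual ventilation as an alternative. Table 1 records abandoned intubation attempts. Entry is therefore a post-allocation event.

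**Step 3. Is entry compared by arm in any stated analysis?** Statistical methods {20a} models enrolled patients with covariates and region effects. The sensitivity analyses in {20c} concern missing data and protocol adherence. Neither compares who entered.

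**Step 4. How large could the bias be?** The plan has no figure to reproduce; Sample size {14} reports no calculation. The following is an illustration with no true treatment effect.

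Inputs: ROSC 30%, the upper end of the usual range quoted in the Introduction; 300 per arm, from Sample size {14}. Assumed: the share *m* of would-be patients omitted in one arm, and their ROSC probability *r*.

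Observed ROSC in that arm = (0.30 - *m* × *r*) / (1 - *m*).

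| *m* | *r* = 60% | *r* = 5% |
|---|---|---|
| 5% | (0.30 - 0.03)/0.95 = 28.4% (-1.6 points) | (0.30 - 0.0025)/0.95 = 31.3% (+1.3) |
| 10% | (0.30 - 0.06)/0.90 = 26.7% (-3.3) | (0.30 - 0.005)/0.90 = 32.8% (+2.8) |
| 20% | (0.30 - 0.12)/0.80 = 22.5% (-7.5) | (0.30 - 0.01)/0.80 = 36.25% (+6.25) |

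For scale, the 95% confidence half-width for the difference, ignoring clustering, is 1.96 × √(2 × 0.3 × 0.7 / 300) = 7.3 points.

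**Step 5. A second scenario.** Suppose instead that a share *k* of would-be non-ROSC patients is omitted in one arm. Observed ROSC = 0.30 / (0.30 + 0.70 × (1 - *k*)), and the odds ratio is 1/(1 - *k*). The rejection rate is for a two-sided 5% two-proportion z-test that ignores clustering; the 5% level is also an assumption.

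| *k* | Observed ROSC | Odds ratio | Rejection rate with no true effect |
|---|---|---|---|
| 5% | 31.1% | 1.05 | about 6% |
| 10% | 32.3% | 1.11 | about 9% |
| 20% | 34.9% | 1.25 | about 23% |
| 30% | 38.0% | 1.43 | about 49% |

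Small differential selection does little; 20 to 30% would produce an apparent effect where none exists.

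**The case against.** The strongest reply is that nothing is hidden and little is likely to go wrong. Section {17a} says that crews are unblinded, and the programming and stickers serve to prevent unintended crossover. The phrase about access before assignment can be read at region-period level, where it may be correct. Participant timeline {13} places the intervention immediately after the airway is secured, which reads as a routine step, and each region serves both arms. The trial is a pilot, and table detail may sit in an analysis plan that is not shown.

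Much of this stands, and it rules out several stronger readings that a reader might infer:

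- *That the concealment claim should be deleted.* Region-level concealment may be sound, so the claim needs narrowing.
- *That crews are free to continue with bag ventilation.* This is inferred. No section makes mechanical ventilation mandatory, but none describes a free choice either.
- *That unventilated patients are absent from the data, so selection could never be detected.* Study setting {9} and the eCRF statement under Additional considerations suggest that they may be recorded. The supportable point is that no comparison using them is stated.
- *That Study setting {9} defines a rival trial population.* Read literally, it would also admit children and trauma cases, which the exclusions remove. It is loose wording that needs reconciling.

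What does not stand is the wording of {16b}, which claims concealment throughout enrolment and is contradicted by the last sentence of the same section. Pilot status does not remove the issue either, since the effect estimate is meant to carry forward.

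**Conclusion.** The concealment claim in {16b} is wrong at patient level; only the region-level sequence before implementation can be called concealed. Entry passes through an action of unblinded crews, so the analysed set is formed after allocation and could differ by arm, and no stated analysis examines this.

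A reader might go on to infer that the ROSC comparison is biased. The documents do not show that. The illustrated shifts of -3.3 and +2.8 points rest on an assumed 10% omission in one arm and assumed ROSC of 60% or 5% in those omitted. They are under half the 7.3-point half-width. A shift of about that half-width needs roughly 20% omission with a marked difference in prognosis. This is a point that should be fixed, not one that invalidates the design.

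**What to change.** 1. In {16b}, limit the claim to the region-level sequence before implementation, and state that crews know the arm when they enrol.
2. Reconcile the population wording in Study setting {9} and Additional considerations with the ventilation criterion in Eligibility criteria {10}, and say whether unventilated cases are recorded in the eCRF.
3. From the eCRF, or from the standard EMS documentation named in Data management {19}, count all adult non-traumatic OHCA with attempted resuscitation in each region-period. Report by arm the share mechanically ventilated, with age, initial rhythm, witnessed status and ROSC.
4. Add a sensitivity analysis of ROSC by allocated period in all these patients, whether or not they were ventilated.

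The cost is one records extract per region and one extra model. Because it can draw on routine records, it remains feasible although recruitment has started (Trial status). The downside is that including patients who never received the allocated setting dilutes any effect, so this stays a sensitivity analysis beside the primary one.

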### Implementation {16c}

The allocation sequence will be generated by the study’s central coordinating team. EMS personnel in the participating regions (Gütersloh, Minden-Luebbecke, and Osnabrueck) will be responsible for enrolling participants based on eligibility criteria. However, the actual assignment of participants to the PEEP or ZEEP group will occur automatically according to the pre-determined allocation sequence managed by the central team.

## Assignment of interventions: blinding

### Who will be blinded {17a}

In this study, the EMS personnel delivering the interventions (PEEP or ZEEP) will not be blinded, as they need to know which ventilation strategy to apply during resuscitation. Since the patients enrolled in the study are unaware of which group they are assigned to during the resuscitation, they are considered blinded.

However, the outcome assessors and data analysts who evaluate the results, including ROSC probabilities and other clinical outcomes, will be blinded to the group assignments to minimize bias in data interpretation and analysis.

This blinding ensures that the analysis is conducted without any knowledge of which intervention was applied, maintaining objectivity in assessing the study’s outcomes.

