### Outcomes {12}

Primary outcome:

The primary outcome is return of spontaneous circulation (ROSC), defined according to the Utstein template as the presence of a palpable carotid or femoral pulse during or after resuscitation, optionally confirmed by Doppler or ultrasound when available [9].

ROSC will be measured as a binary variable (yes/no), and the analysis will compare the proportion of patients achieving ROSC between the two study groups (PEEP vs. ZEEP).

This definition ensures consistency with international reporting standards and enhances the reliability of outcome assessment.

Secondary outcomes:oRe-Arrest-RateoDeath during pre-hospital care phaseoHospital admission during ongoing resuscitationoHospital admission with spontaneous circulationoSpO_2_ at hospital admissionoFiO_2_ at hospital admissionoetCO_2_ at hospital admissionOther outcomes:oDate of death (if applicable), analyzed as a time-to-event outcome, focusing on survival duration post-resuscitation.oDate of hospital discharge for survivors, measured as time to discharge.oNeurological status, measured as the Cerebral Performance Category at hospital discharge.

These outcomes are relevant as they provide a comprehensive assessment of both immediate and longer-term clinical effects of the interventions. ROSC is vital for short-term survival, while neurological status and vital signs reflect the quality of resuscitation and longer-term outcomes. Time to death and discharge further provide insight into survival and recovery rates.

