## Data collection and management

### Plans for assessment and collection of outcomes {18a}

Data acquisition will be carried out using an eCRF, which is to be completed by the emergency care team following the resuscitation. The data collected will be supplemented with the ventilation parameters recorded by the emergency ventilators. The variables collected in the eCRF are shown in Table 1.

**Table 1 Tab1:** Variables collected in the eCRF

Category	Collected variables
Patient factors	Age (years), Sex, Comorbidities
Airway factors	Bag-mask ventilation before airway device placement (yes/no), Intubation (extraglottic airway device vs. endotracheal tube), Type of extraglottic airway device, Number of insertion attempts, Complications during insertion, Number of intubation attempts, Complications during intubation, Abandonment of intubation attempts, Re-intubation by emergency physician
Resuscitation data	Observed cardiac arrest (yes/no), Cardiac arrest observed by (layperson/emergency services), Layperson CPR performed (yes/no), Time to initiation of chest compressions, Resuscitation duration (minutes), Initial ECG findings, Defibrillation (yes/no), Number of defibrillations, Type of chest compressions (manual vs. mechanical), Type of mechanical compression device, Administration and cumulative dose of epinephrine and amiodarone
Intra-arrest ventilation data	Ventilation parameters set by emergency services (Pmax, PEEP, respiratory rate, tidal volume, inspiration-expiration ratio, FiO_2_, Ventilation mode: IPPV, BILevel, CCSV, Other), Ventilation parameters measured by Medumat Transport, Changes in ventilation parameters during resuscitation
Post-arrest treatment	Re-intubation from extraglottic airway to endotracheal tube (yes/no), Number of intubation attempts, Type and dose of analgesic, hypnotic, muscle relaxant, Complications in pre-hospital post-arrest phase (aspiration, ventilation issues, hypotension, re-arrest), Administration of catecholamines, Post-arrest ventilation settings
Additional outcome data	Consciousness at handover, ECG findings at handover, Glasgow Coma Scale, Vital parameters at handover (systolic blood pressure, heart rate, oxygen saturation, respiratory rate, etCO_2_), Initial blood gas analysis, Date of death, Hospital discharge date

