## Oversight and monitoring

### Composition of the coordinating center and trial steering committee {5d}

The coordinating center is comprised of a central team responsible for day-to-day management, operational support, and data coordination. This team ensures that all study procedures are implemented according to the protocol and meets regularly to monitor progress.

In addition, the trial steering committee provides overall oversight, strategic guidance, and ensures adherence to the study protocol. This committee meets at predetermined intervals throughout the trial to review progress and address any issues. Supporting groups, such as the endpoint adjudication committee and the data management team, are also involved in maintaining data quality and trial integrity.

It is important to note that no interim analyses are planned during the course of the trial.

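### Section {17a} claims blinded outcome assessment for ROSC, but by the only data route described the unblinded crew determines and records it; the claim can hold for analysis, not for ascertainment

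*Protocol article*

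**What the plan says.** Section {17a} makes two statements. First, "the EMS personnel delivering the interventions (PEEP or ZEEP) will not be blinded". Second, "the outcome assessors and data analysts who evaluate the results, including ROSC probabilities and other clinical outcomes, will be blinded to the group assignments". It gives the purpose of the second as reducing bias in interpreting and analysing the data, and it closes by saying that the blinding has the effect of "maintaining objectivity in assessing the study’s outcomes".

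Outcomes {12} defines the primary endpoint as "the presence of a palpable carotid or femoral pulse during or after resuscitation, optionally confirmed by Doppler or ultrasound when available", recorded as yes or no. Section {18a} says that data are acquired through an "eCRF, which is to be completed by the emergency care team following the resuscitation", supplemented by ventilation parameters read from the ventilators. Table 1 in that section shows that the eCRF also holds the set and measured ventilation parameters, with PEEP among the settings.

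The Discussion says that training sessions and stickers on the ventilators are meant to tell crews which group a patient is in. Section {16b} says that staff are regularly informed of the current assignment.

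On oversight, {5d} adds: "Supporting groups, such as the endpoint adjudication committee and the data management team, are also involved". The article does not say what this committee reviews, from which records, or whether it is masked.

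**The concern.** A blinded-assessor statement tells the reader that whoever decided whether the endpoint occurred did not know the arm. For ROSC that decision is a bedside judgement made during resuscitation, and the people at the bedside set the ventilator to the assigned arm. If doubtful pulses are recorded as ROSC more readily in one arm, the difference enters the data before any analyst or committee sees them, and later masking cannot remove it.

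Two things are at stake. The trial report would carry an incorrect risk-of-bias statement for its primary endpoint. The ROSC effect estimate, which Sample size {14} intends as an input to a future confirmatory trial, would be passed on without the caution it needs.

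**Working it through.** **Step 1: who determines ROSC.** The passages, side by side:

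- {12}: the endpoint is a pulse felt at the carotid or femoral artery. Doppler or ultrasound is optional.
- {18a}: the treating team completes the eCRF afterwards. The other pre-hospital source is the ventilator read-out, which supplies ventilation parameters and not a pulse.
- {17a}, {16b} and the Discussion: that team is unblinded and is deliberately kept informed of the arm.

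No sentence says outright that the crew palpates the pulse, and Table 1 has no separate ROSC field. The inference rests on the setting and on there being no other described source.

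**Step 2: whether the adjudication committee restores blinding.** A pulse felt at the scene cannot be felt again, so a committee can only review what the crew recorded. As Table 1 stands, that record includes set PEEP. Under {16a} each region has one arm for 6 months and then the other, so region and date also identify the arm to anyone who knows the sequence. Masked review is possible with a suitable extract. It would be blinded review of an unblinded record, not blinded ascertainment.

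**Step 3: what a small recording bias would do (illustration only).** The protocol gives no figure to reproduce: {14} states that no power calculation was done.

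Inputs from the document: n = 300 per arm ({14}); ROSC p = 30% and 50%, the two rates mentioned in Background and rationale {6a}. Assumptions: no true effect, two-sided test at 5%, no clustering, and b extra points of recorded ROSC in the PEEP arm only.

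Formulas, with p1 = p, p2 = p + b and m = (p1 + p2)/2:

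- SE0 = sqrt(2m(1 − m)/n)
- SE1 = sqrt(p1(1 − p1)/n + p2(1 − p2)/n)
- Rejection probability = Φ((b − 1.96·SE0)/SE1) + Φ((−b − 1.96·SE0)/SE1)

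For p = 0.30 and b = 0.03: m = 0.315, SE0 = 0.03793, SE1 = 0.03791. The upper tail is Φ((0.03 − 0.07434)/0.03791) = Φ(−1.17) = 0.121. The lower tail is Φ(−2.75) = 0.003. The total is 12.4%.

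| Extra recorded ROSC in PEEP arm | Patients of 300 | False-positive rate, ROSC 30% | False-positive rate, ROSC 50% |
|---|---|---|---|
| 0 points | 0 | 5.0% | 5.0% |
| 2 points | 6 | 8.3% | 7.8% |
| 3 points | 9 | 12.4% | 11.4% |
| 5 points | 15 | 25.7% | 23.2% |

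A 3-point excess corresponds to recording 0.03/0.70 = 4.3% of non-ROSC patients as ROSC when the true rate is 30%, or 0.03/0.50 = 6% when it is 50%. It produces an apparent odds ratio of (0.33/0.67)/(0.30/0.70) = 1.15 or (0.53/0.47)/(0.50/0.50) = 1.13 with no true effect.

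**The case against.** The strongest reply is that {17a} limits its own claim. It states openly that the crews are unblinded, ties the blinding to interpretation and analysis, and speaks of ROSC probabilities, which are group-level results. On that reading its outcome assessors are evaluation-stage staff and nothing is contradicted. Part of this stands: blinded analysis is a coherent claim and can be kept. The reading does not cover the whole text, because {17a} also names outcome assessors separately from analysts and claims objectivity in assessing outcomes. A reader will take that as blinded endpoint assessment.

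A second reply is that an endpoint adjudication committee exists and that its remit may be in governance papers that are not shown. That is possible, and the missing detail is not itself the fault. Even so, the committee would depend on the crew's record (step 2).

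A third reply is that this is a pilot that states no alpha and is not meant to establish superiority, so a false-positive rate has limited bearing. This is fair as to weight. The bias would equally distort the effect estimate that the pilot is meant to supply.

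Three stronger readings are tempting, and the documents do not support them:

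- A reader might infer that crews are taught to expect PEEP to help. The training described covers study procedures and the current assignment, and {6a} itself says that PEEP may reduce cardiac output. The direction of any bias is therefore assumed.
- A reader might infer that the analysts are unmasked too. That depends on the data extract they receive, which the article does not describe, and on whether they know the centrally held sequence.
- A reader might infer that the crews should have been blinded. They have to set the ventilator, so this is not achievable here.

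**Conclusion.** The point holds for ascertainment of the primary endpoint. Section {17a} claims a protection for ROSC that the described data route does not provide. The claim can stand for data analysis, and the lack of crew blinding is not a defect in itself.

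The size of any bias is unknown. The rise from 5% to about 11–12% for a 3-point over-recording rests on the assumptions in the working: one-directional misrecording, no true effect, 300 per arm, two-sided 5% and no clustering. It shows that about 9 of 300 patients would be enough to matter; it does not estimate what will happen in this trial. The conclusion about blinding does not depend on that arithmetic.

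**What to change.** 1. Reword {17a} to say that ROSC is determined and recorded by unblinded EMS crews, and limit the blinding claim to analysts and adjudicators.
2. Say how analysts are masked: coded arm, set and measured PEEP withheld, and region codes kept consistent so that the region random effect in {20a} can still be fitted.
3. Have the committee named in {5d} review recorded ROSC against the etCO2 and handover data already collected, with PEEP, region and date removed. Use this as a sensitivity analysis, leaving the Utstein primary definition unchanged.
4. Report hospital admission with spontaneous circulation, already a secondary outcome, beside ROSC as a less judgement-dependent supportive result. No rule that the two must agree is needed. It should not be called hospital-verified, because the article describes no such verification and the handover data sit in the crew-completed eCRF.
5. State ascertainment bias in ROSC as a limitation.

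The cost is a wording change, a masked data extract and some committee time, all of which can be done before analysis. No new measurement and no change to patient care is involved.
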